## Abstract

*Background*. In the past, moxibustion has been widely used to treat endocrine system disorders, but evidence of its effectiveness is scarce at this point. The aim of this multicenter, randomized, controlled trial is to evaluate the efficacy and safety of treating menopausal obesity with moxibustion. *Methods/Design*. There are six centers taking part in this randomized, controlled, parallel trial. A total of 216 patients with menopausal obesity will be randomly divided into two equal groups: the “moxibustion for harmonization of Yin and Yang” group and the gentle moxibustion group. A 12-week study period with moxibustion will be preceded by a 1-week baseline, followed by a 12-week follow-up. We will conduct an interim analysis to determine whether or not the treatment is efficacious and safe after 216 participants have completed a 12-week treatment period. Evaluations will be conducted at weeks 0, 4, 8, 12, 18, and 24. The main outcome is waist circumference (WC), and the rate of WC reduction will be compared to the baseline. An intention-to-treat analysis will be performed with a two-sided *P* value of <0.05 considered significant. Participants who withdraw from the trial will be analyzed according to the intention-to-treat formula (ITT). *Discussion*. These results will be used to support selecting the right moxibustion prescription and guiding the improvement of clinical efficacy. This trial will provide convincing evidence of moxibustion's effectiveness and safety in the treatment of obesity by “moxibustion for harmonization of Yin and Yang,” which will be conducive to the promotion and clinical application of the theory of “moxibustion for harmonization of Yin and Yang.” *Trial Registration*. This trial is registered with Clinical Trials.gov: NCT04943705 (registered on June 27, 2021).

## 1. Introduction

Obesity is a multifactorial condition caused by genetic, physiologic, behavioral, sociocultural, and environmental factors that lead to an imbalance between energy consumption and expenditure over a long period of time [1]. According to the Global Burden of Disease Obesity Collaborators, 603.7 million adults worldwide suffer from obesity [2], and the global prevalence of overweight or obesity ranges from 39% to 49% [3], with morbidity doubling between 1980 and 2015 in 73 countries. In addition to significantly decreasing the quality of life of patients, obesity is associated with an increased risk of illness (such as diabetes, hypertension, and cardiovascular disease) and mortality [1, 4, 5]. Moreover, it causes mental illnesses (e.g., depression, unwarranted stigma, and schizophrenia) and increases health care costs in countries all over the world [6–8]. Menopause is characterized by an increase in FSH levels [9]. This is a time when women are susceptible to gaining a great deal of visceral fat due to increased glucocorticoid secretion and increased glucocorticoid secretion, among other factors [10, 11]. A woman who is obese at menopause may also have an increased risk of developing breast cancer, endometrial and colon cancer, type 2 diabetes, and cardiovascular disease [12]. In a meta-analysis [13], obesity is associated with a 25% to 30% relative increase in breast cancer-specific and overall mortality among menopausal women.

At present, the main intervention methods for obesity include lifestyle intervention, western medicine treatment, bariatric surgery, and traditional Chinese medicine therapy [14]. A simple diet and exercise method is often difficult to adhere to and easy to rebound [15]. Western drugs for weight loss need clear indications, and long-term safety studies for weight loss drug therapy are lacking [16]. Multiple randomized controlled trials have reported bariatric surgery's effectiveness in treating obesity, but it also carries a greater risk of cardiovascular disease and mortality and is costly [17]. Consequently, seeking safe and effective therapies for menopause obesity prevention and control has become an increasingly important concern.

Moxibustion, as a green therapy for weight loss because of its safe operation, outstanding curative effect, low cost, and good patient compliance, has become a popular treatment option for obese patients in recent years. Numerous studies indicate that moxibustion is efficient in relieving menopausal symptoms by enhancing the immune system and altering the amounts of neurotransmitters in the central nervous system through repeatedly stimulating acupoints[18, 19]. As far as we know, by applying moxa to warm acupoints and body areas, moxibustion can promote a smoother flow of qi and blood in the human body[20]. This increases blood circulation generally, which has the benefits of illness prevention and health care. By activating beige fat via the HSF1-A2B1 transcriptional axis, moxibustion can be utilized to treat obesity through local thermal stimulation[21]. It is acknowledged that menopausal obesity is caused by the imbalance of Yin and Yang according to the theory of etiology and pathogenesis of traditional Chinese medicine. Based on this, our research group innovatively apply “moxibustion for harmonization of Yin and Yang” to treat menopause obesity, so as to restore the balance between Yin and Yang. Compared with ordinary moxibustion, “moxibustion for harmonization of Yin and Yang” achieves coverage from point to surface. As for moxibustion quantity, it has a wider range of treatment and higher comfort. The frequency of moxibustion is usually once a week, which saves the time cost of patients' medical treatment and is more convenient. In sequence and position of moxibustion, double-sided moxibustion with the Yang side before the Yin side promotes spontaneous harmonization of Yin and Yang. However, for menopausal obesity, due to hormone levels, psychological state, and other reasons, the curative effect of moxibustion is often unable to be unified. There have not been many studies comparing various moxibustion techniques side by side to see how effectively they vary.

The Study of Women's Health Across the Nations (SWAN) [22], an observational cohort of menopausal female followed for over a decade, have suggested that after the onset of menopause, due to estrogen loss, women often continue to have bone loss, disrupted energy balance, and reduced physical activity and further accrue visceral fat, resulting in obesity [23]. Modern studies have shown that [24, 25] moxibustion can improve immunoglobulin and reduce proinflammatory cytokines and promote energy metabolism. It also has the effect of regulating nerves, anti-inflammatory properties, enhanced immunity, and accelerated metabolism.

Therefore, this multicenter randomized controlled research is on the variations in effectiveness between the two moxibustion prescriptions for treating menopausal obesity by assessing the safety, efficacy, and health economic evaluation of the “moxibustion for harmonization of Yin and Yang” compared to the gentle moxibustion, in order to increase the therapeutic impact and give high-quality evidence-based evidence for a better choice of moxibustion prescription.

## 2. Methods and Design

### 2.1. Objectives

This study aims to (1) assess the effectiveness and security of moxibustion in the treatment of menopausal obesity; (2) compare the safety, efficacy, and health economic evaluation of different moxibustion methods for treating menopausal obesity, so as to optimize the prescription of moxibustion; and (3) investigate the effect of moxibustion in ameliorating the metabolism and relieving symptoms of menopause.

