### 2.2. Study Design

This will be a multicenter, randomized, controlled, two-arm clinical trial, where 216 participants will be randomized at a ratio of 1 : 1 to two groups (108 participants per group). There are six academic hospitals in China where this study will be carried out: Hubei Provincial Hospital of TCM, Shanxi Provincial Hospital of TCM, Shenzhen Baoan Hospital of TCM (Group), Xiamen Hospital of TCM, Jiangsu Provincial Hospital of TCM, and the First Affiliated Hospital of the Hunan University of TCM. A 12-week treatment phase plus a 12-week follow-up period make up the 24-week duration of this research. If they are qualified for the study, each participant is required to keep a diet and exercise diary for the whole research cycle. All participants will receive 12 weeks of individual treatments in two groups: the “moxibustion for harmonization of Yin and Yang” will be administered once every 1 week, 60 minutes each time; the gentle moxibustion will be administered 3 times a week, 20 minutes each time. Outcomes will be assessed at the beginning, at the conclusion, and during the follow-up period. The Standard Protocol Items: Recommendations for Intervention Trials (SPIRIT) [26] are utilized in the protocol, which is based on the Standards for Reporting Interventions in Clinical Trials of Acupuncture (STRICTA) [27](Additional file 1).  Figure 1 provides a summary of the trial's design.

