### 2.7. Interventions

#### 2.7.1. Lifestyle Modification

Both groups of patients get lifestyle intervention, with the following suggested living habits [31]: all individuals weighing 113.6 kg (250 lb.) will be provided a diet of 1200 to 1499 kcal/day consisting of standard foods with roughly 20% to 35% kcal from fat, 15% to 20% kcal from protein, and the remaining from carbohydrate. Those weighing 113.6 kg will be prescribed a diet of 1500 to 1800 kcal/day. Meanwhile, all participants will be instructed to keep a daily food and calorie diary, and they will be instructed to engage in low-to-moderate intensity physical activities such as jogging and walking for at least 5 days per week and for at least 210 minutes per week, preferably 270 minutes per week.

All patients will be required to keep a diet and exercise diary at least 4 days per week. The intervention time for lifestyle intervention includes a 12-week treatment phase and a 12-week follow-up period.

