### 2.11. Statistical Analysis

SAS 9.3 software will be used by an impartial statistician to analyze the data (SAS Institute Inc, Cary, NC). Any participant who completes the randomized stage and receives at least one intervention will be analyzed using a full analysis set (FAS), with missing data for the important outcomes interpolated with the last observation carried forward, in accordance with the intention-to-treat (ITT) analysis strategy. Multiple imputations will be used to deal with missing data. All statistical inspections were used for bilateral testing, and statistical significance will be determined at *P* < 0.05.

For the patient's missing data, it is assumed that the deletion data is randomly missing, the lacking value of the research main indicator is used for multiple filling methods, the stochastic missing deletion assumption of multiple filling is performed, and the stability test of the missing data filling results is carried out by using pattern mixture model (PMM). The measurement data is described by average ± standard deviation ($\bar{x}\pm S$), median, maximum, and minimum, and the counting data and grade data are described by cases and percentages. Intergroup comparison will select the analysis method according to the data distribution feature: the measurement data is used to test or nonparameter testing; the count data is used in*χ*^2^inspection or Fisher's exact probability method, and the grade data is used in the nonparameter test. Compared with the baseline value, the metering data is used in pair*T*inspection or nonparameter test, and counting materials use nonparameter test.

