## 3. Discussion

The NCD risk factor collaboration [33] has shown that obesity is a significant worldwide health problem with a rise in prevalence from 3.1% in 2014 to 8.1% in 2018 [34]. It is estimated that 85 million Chinese adults aged 18–69 were obese in 2018 [35]. At present, the research on the treatment of obesity at domestic and abroad levels is mainly concentrated on acupuncture therapy, electroacupuncture, acupoint embedding, etc., with less research on moxibustion [36, 37]. Moxibustion, which comes in a variety of forms and is one of Traditional Chinese medicine's external therapeutic modalities, has been proved to be useful in the management of obesity [38–41], but it is considered to be a complementary therapy to acupuncture, which is usually used in combination with other therapeutic methods in clinical practice, resulting in the superiority of moxibustion being not fully realized. So far, few clinical trials have been conducted to confirm the efficacy and safety of moxibustion therapies for menopausal obesity. This is the first randomized controlled trial focusing on the variations in the effectiveness of “moxibustion for harmonization of Yin and Yang” compared to the gentle moxibustion for treating menopausal obesity. The outcomes will present evidence for better clinical effectiveness and prescription choice for moxibustion. Additionally, the outcomes of this experiment will be utilized to verify the safety and efficacy of the “moxibustion for harmonization of Yin and Yang” in regard to menopausal obesity treatment and provide high-level evidence-based evidence supporting the use of “moxibustion for harmonization of Yin and Yang” in the therapeutic treatment of menopausal obesity.

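### Objectives 1 and 3 claim an effect of moxibustion as such, but both arms receive moxibustion on the same diet and exercise programme, so the trial can only compare two regimens

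*Protocol article*

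**What the plan says.** Section 2.1 lists three aims. The first is to "assess the effectiveness and security of moxibustion in the treatment of menopausal obesity". The second is the comparison of the moxibustion methods. The third is to "investigate the effect of moxibustion in ameliorating the metabolism and relieving symptoms of menopause". Aims 1 and 3 speak of moxibustion itself; only aim 2 is comparative.

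Section 2.2 describes two arms with 1:1 allocation. The Yin-Yang arm has one 60-minute session a week. In the comparator arm, "the gentle moxibustion will be administered 3 times a week, 20 minutes each time". Sections 2.7.2 and 2.7.3 confirm that both are active moxibustion. No sham, waiting-list or lifestyle-only arm is described.

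Section 2.7.1 adds: "Both groups of patients get lifestyle intervention". This is a calorie-limited diet (1200–1499 or 1500–1800 kcal/day), at least 210 minutes of exercise a week, and a diary. It runs through treatment and follow-up, 24 weeks in all.

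Section 2.11 names between-group comparisons and then tests against baseline: "Compared with the baseline value, the metering data is used in pair" (a paired t test or a nonparametric test).

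On conclusions, the Abstract promises persuasive evidence that moxibustion is effective and safe in obesity. Section 3 says that "the outcomes of this experiment will be utilized to verify the safety and efficacy of the" Yin-Yang regimen, and its closing paragraph promises an evaluation of the efficacy of various moxibustion treatments.

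**The concern.** An absolute effect of moxibustion is a contrast with the same care without moxibustion, and nobody in this trial receives that care. A change from baseline in either arm combines moxibustion, diet, exercise, diary keeping, attention and the passage of time. Randomisation balances these between the arms but does not remove them from the within-arm change.

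What is at stake is the conclusion. If the arms do not differ, the trial cannot tell two effective regimens from two ineffective ones. If the Yin-Yang arm is better, the randomised evidence is for a relative advantage over gentle moxibustion. A significant fall from baseline in both arms could be reported under objective 1 as showing that moxibustion works, although the lifestyle programme alone could produce it.

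**Working it through.** **What the design identifies.** Write the expected waist reduction in each arm as an additive sum, where L is everything shared (diet, exercise, time) and m is the effect of that arm's moxibustion:

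- Yin-Yang arm: D1 = m1 + L
- Gentle arm: D2 = m2 + L
- Difference: D1 − D2 = m1 − m2

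There are two observable means and three unknowns. At the planning values in section 2.9 (D1 = 6.15 cm, D2 = 3.94 cm) the difference is 6.15 − 3.94 = 2.21 cm, whatever L is:

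| Assumed L (cm) | m1 = 6.15 − L | m2 = 3.94 − L | m1 − m2 |
|---|---|---|---|
| 0 | 6.15 | 3.94 | 2.21 |
| 2 | 4.15 | 1.94 | 2.21 |
| 3.94 | 2.21 | 0 | 2.21 |

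The same data fit gentle moxibustion being worth 3.94 cm or nothing. The protocol gives no lifestyle-only figure that would fix L.

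**The plan's own sample size.** Section 2.9 states 96 per group at one-sided α = 0.025 and 80% power.

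- Pooled SD = √[(1.56² + 1.14²)/2] = 1.366 cm.
- n per group = 2 × (1.960 + 0.842)² × 1.366² / 2.21² ≈ 6. This is not 96.
- For 96 to follow at a difference of 2.21 cm, the SD would have to be about 5.5 cm.
- Dropout: 96/0.9 = 106.7, so 107, close to the stated 108.

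The mismatch is a separate matter. It is relevant here only because it makes the planning SDs doubtful, so larger SDs are also shown below.

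**How sensitive a within-arm paired test is.** With n = 96, √96 = 9.798. The mean change detectable with 80% power at two-sided 5% is about 2.802 × SD/√96:

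- SD 1.14: 2.802 × 1.14/9.798 = 0.33 cm
- SD 1.56: 2.802 × 1.56/9.798 = 0.45 cm

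**Illustration with zero moxibustion effect.** Set m = 0 and let the whole change be L. The chance of significance comes from the noncentral t distribution with 95 degrees of freedom and noncentrality L√96/SD. For L = 0.5 cm the noncentrality is 0.5 × 9.798/1.56 = 3.14 or 0.5 × 9.798/1.14 = 4.30.

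| SD of change (cm) | Source | L = 0.25 | L = 0.5 | L = 1 | L = 2 |
|---|---|---|---|---|---|
| 1.14 | section 2.9, gentle arm | 0.57 | 0.99 | 1.00 | 1.00 |
| 1.56 | section 2.9, Yin-Yang arm | 0.34 | 0.87 | 1.00 | 1.00 |
| 4 | assumption | 0.09 | 0.23 | 0.68 | 0.998 |
| 6 | assumption | 0.07 | 0.13 | 0.37 | 0.90 |

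All values of L are assumptions.

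**The case against.** An active comparator on shared background care is a legitimate design, and the protocol often frames the trial that way. The last paragraph of the Introduction speaks of differences in effectiveness between two prescriptions, objective 2 is comparative, and section 2.9 sizes the trial from the two arms' improvements. This stands: the fault lies in the absolute wording placed on the design, not in the design itself.

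Section 2.11 does not link the paired tests to objective 1 or call them efficacy evidence. A reader might infer that the plan intends them as proof of efficacy; the text does not say so. What can be said is that no other named analysis could address an absolute effect.

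A reader might also infer that both paired tests are practically certain to be significant even if moxibustion does nothing. The documents do not support that. At the planning values the paired t statistics are 3.94/(1.14/√96) ≈ 34 and 6.15/(1.56/√96) ≈ 39, but those improvements were planned with moxibustion, so they are not a zero-effect case. Under zero effect the answer depends on a lifestyle change that the protocol does not give and on SDs that are doubtful; the table runs from 0.07 to 1.00. Regression to the mean after entry at a waist of 80 cm or more is possible, but its size is unknown because no baseline distribution is given, and the argument does not need it.

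It could also be said that a Yin-Yang advantage would imply an absolute benefit of that regimen. That follows only if gentle moxibustion is assumed not to worsen the outcome, which this trial does not test.

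Finally, objective 1 also covers safety. Adverse events such as burns and blistering (section 2.12) are usefully described per arm, so that part should not be recast as a comparison only. A fuller analysis plan may already label the within-arm tests descriptive, but no analysis plan can supply a contrast that the design lacks.

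**Conclusion.** The point holds in this form: the efficacy part of objective 1, and objective 3, state an absolute effect of moxibustion that this two-arm trial cannot identify, and the Abstract and section 3 carry that claim into the conclusions. Within-arm tests cannot fill the gap, because they mix moxibustion with a 24-week lifestyle programme and time.

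This rests only on the described arms and co-intervention. The illustration adds scale under stated assumptions: with no moxibustion effect and 96 in an arm, a 0.5 cm shared change is significant 87 to 99% of the time at the protocol's SDs. At SDs of 4 to 6 cm the figures are 37 to 68% for 1 cm and about 90% or more for 2 cm. The conclusion would be the same if those probabilities were lower. It is a correctable fault of wording and interpretation; the randomised comparison of the two regimens is unaffected by it.

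**What to change.** - In section 2.1, restate the efficacy part of objective 1, and objective 3, as comparisons of the Yin-Yang regimen with gentle moxibustion, both added to lifestyle intervention. The Introduction already has suitable wording.
- Keep a per-arm description of safety under objective 1.
- In section 2.11, state that changes from baseline within an arm are descriptive and will not be used as evidence of efficacy, whether shown as tests or as confidence intervals. An interval that excludes zero invites the same reading as a significant test, so the statement matters more than the format.
- In the Abstract and section 3, including its closing paragraph, limit the efficacy claims to the effect relative to gentle moxibustion.

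No change to treatment, visits or data collection is needed. The cost is a narrower claim: the trial would no longer promise evidence that moxibustion in itself reduces menopausal obesity. To keep that claim, a control group on the same lifestyle programme without moxibustion would be required, which is a different trial.

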### 2.2. Study Design

This will be a multicenter, randomized, controlled, two-arm clinical trial, where 216 participants will be randomized at a ratio of 1 : 1 to two groups (108 participants per group). There are six academic hospitals in China where this study will be carried out: Hubei Provincial Hospital of TCM, Shanxi Provincial Hospital of TCM, Shenzhen Baoan Hospital of TCM (Group), Xiamen Hospital of TCM, Jiangsu Provincial Hospital of TCM, and the First Affiliated Hospital of the Hunan University of TCM. A 12-week treatment phase plus a 12-week follow-up period make up the 24-week duration of this research. If they are qualified for the study, each participant is required to keep a diet and exercise diary for the whole research cycle. All participants will receive 12 weeks of individual treatments in two groups: the “moxibustion for harmonization of Yin and Yang” will be administered once every 1 week, 60 minutes each time; the gentle moxibustion will be administered 3 times a week, 20 minutes each time. Outcomes will be assessed at the beginning, at the conclusion, and during the follow-up period. The Standard Protocol Items: Recommendations for Intervention Trials (SPIRIT) [26] are utilized in the protocol, which is based on the Standards for Reporting Interventions in Clinical Trials of Acupuncture (STRICTA) [27](Additional file 1).  Figure 1 provides a summary of the trial's design.

### 2.3. Recruitment

we will create a public recruiting advertisement in newspapers, posters, WeChat, or the Internet and seek any patients who fit the requirements. Patients' eligibility to take part in this study will be decided by the doctor. Each patient will have enough time to decide whether or not to take part in the research. And each participant will be required to sign a freely completed written informed consent form. It informs patients about connected clinical research in terms that patients or their legal representatives may comprehend, including explanations of the study purpose, research technique, and procedure.

